### Measurements, outcomes, instruments and procedure

#### Primary outcome—feasibility

Feasibility of the protocol will be assessed using adapted feasibility metrics. These metrics include process, resource, management and scientific metrics.^36 37^ Details on the primary outcomes are summarised in online supplemental table S2.

#### Profiling-related outcome—psychosocial lifestyle profile

Participants will be categorised in psychosocial lifestyle profile based on the number of deviating psychosocial lifestyle factors deducted from scores on the PSQI, DASS-21 and HIT-6. Individual scores will be compared with normative data.^17^ Scores indicating at least: moderate depression, anxiety, stress (DASS-21), headache has a significant impact on daily life (HIT-6), and/or poor sleep quality (PSQI) will be considered as deviating.

##### Psychosocial lifestyle factors

S*leep quality* will be assessed via the Dutch PSQI, a standardised, valid, and reliable self-reported 1 month recall questionnaire.^38 39^ The index differentiates poor from good sleepers by measuring: subjective sleep quality, sleep latency, sleep duration, habitual sleep efficiency, sleep disturbances, use of sleeping medication, and daytime dysfunction. Scores on each of these components vary from 0 (‘No problem’) to 3 (‘Serious problem’). A maximum score exceeding 5/21 indicates poor sleep quality.^40 41^ See Mollayeva *et al* for information on the psychometric properties.^38^

The degree of *depression, anxiety and stress* will be estimated by the Dutch DASS-21.^42 43^ The DASS-21 is a self-reported, 1-week recall questionnaire. Each of the three subscales contains seven items. The depression subscales assess dysphoria, hopelessness, devaluation of life, self-deprecation, lack of interest, anhedonia and inertia. The anxiety subscale estimates autonomic arousal, skeletal muscle effects, situational anxiety and subjective experience of anxious affect. The stress subscale evaluates difficulty in relaxing, nervous arousal, being easily upset and impatience. Items are scored on a Likert scale (0=‘did not apply to me at all’ and 3=‘applied to me very much or most of the time’). Scores of 14, 10 and 19 indicate at least moderate depression, anxiety and stress, respectively. See Lovibond *et al* for information on the psychometric properties.^44^

Impact *of headache on quality of life* will be estimated by the Dutch HIT-6.^45 46^ The HIT-6 evaluates the impact of headache on daily activities: the ability to function at work, school, home and in social situations. Items are scored 6, 8, 10, 11 and 13 (6=‘never’, 8=‘rarely’, 10=‘sometimes’, 11=‘very often’ and 13=‘always’). Scores exceeding 56 indicate headache has a significant impact on daily life.^46 47^ See Martin *et al* and Kosinski *et al* for information on the psychometric properties.^46 48^

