### Statistics

Primary analyses will report results relating to outcomes on feasibility. Descriptive statistics and content analysis will be used to assess feasibility of the protocol. The feasibility study will provide useful information with regard to planning, testing study procedures (eg, estimation of the recruitment rate, plausibility of multicentre collaborations, etc), and investigating outcomes to support adequate sample size calculation.^73^ Data from the CMP and TSP measurements will be used to estimate post hoc sample size (G*Power V.3.1.9.4, Kiel Germany) for a larger trial.

Individual PMPs of at least 12 participants with CeH will be mapped based on the methods outlined in the Profiling-related outcome—psychosocial lifestyle profile and conditioned pain modulation sections. Secondary analyses will involve an analysis of proportions (%) of the different psychosocial lifestyle profiles and pain profiles. Currently no data are available in people with CeH, therefore a pragmatic approach is proposed based on the work of Julious who recommended 12 participants as the minimum for pilot studies.^74^ Justifications for this sample size are based on rationale about feasibility and precision about the mean and variance.^74^ Both primary and secondary analyses will be used to decide whether the feasibility study should be expanded to a full-scale study. The latter implies registering of the trial in accordance with the WHO Trial Registration Data Set (V.1.3.1).

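### The DASS-21 cut-offs of 14, 10 and 19 come with no stated score scale and fit the 0–21 subscales that the article describes poorly, most clearly for stress

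*Protocol article*

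**What the plan says.** The section Psychosocial lifestyle factors gives three facts about the DASS-21.

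- Item count: "Each of the three subscales contains seven items".
- Item range: "Items are scored on a Likert scale (0=‘did not apply to me at all’ and 3=‘applied to me very much or most of the time".
- Cut-offs: "Scores of 14, 10 and 19 indicate at least moderate depression, anxiety and stress, respectively".

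No summation rule, score range or multiplication is given. The source cited directly after the cut-offs is offered for psychometric properties, not for scoring.

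The section Profiling-related outcome—psychosocial lifestyle profile turns the cut-offs into flags: "Scores indicating at least: moderate depression, anxiety, stress (DASS-21), headache has a significant impact on daily life (HIT-6), and/or poor sleep quality (PSQI) will be" counted as deviating. Participants are then placed in a profile "based on the number of deviating psychosocial lifestyle factors deducted from scores on the PSQI, DASS-21 and HIT-6". In Statistics, the output is descriptive: "Secondary analyses will involve an analysis of proportions (%) of the different psychosocial lifestyle profiles and pain profiles". The number of participants is small: "Individual PMPs of at least 12 participants with CeH will be mapped".

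**The concern.** A reader who scores the questionnaire from this text would sum seven items to a total between 0 and 21 and compare it with 14, 10 and 19. For stress that gives a threshold for moderate close to the ceiling of the scale, which is hard to reconcile with the existence of grades above moderate. This suggests that the cut-offs were set for a different scale, and that a conversion step has dropped out of the description.

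The same section makes the literal reading more likely. The PSQI is described just before, also with seven components scored 0 to 3, and its threshold is read directly against a total of 21. Under Data management plan, paper questionnaires are transferred to spreadsheets, and no scoring step is described there.

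At stake is the psychosocial half of the pain modulation profile. If each DASS-21 subscale counts as one factor, which the article does not spell out, these cut-offs supply three of five possible flags; PSQI and HIT-6 supply the other two. Statistics says that primary and secondary analyses together will inform the decision on a full-scale study. With about 12 participants, moving one person changes a proportion by 1/12, or about 8 percentage points.

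**Working it through.** **Inputs from the article:** 7 items per subscale; item scores 0 to 3; cut-offs 14 (depression), 10 (anxiety) and 19 (stress); at least 12 participants. The article gives no derivation of the cut-offs, so there is no figure to reproduce.

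**Step 1: scale as described.** Maximum of a plain sum = 7 × 3 = 21.

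| Subscale | Cut-off | Share of 21 | Mean item score needed (cut-off/7) |
|---|---|---|---|
| Depression | 14 | 66.7% | 2.00 |
| Anxiety | 10 | 47.6% | 1.43 |
| Stress | 19 | 90.5% | 2.71 |

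**Step 2: what 19 of 21 requires.** With k items at 3 and the rest at no more than 2, the largest possible sum is 3k + 2(7 − k) = 14 + k. For k = 4 this is 18, below the cut-off. For k = 5 it is 19. So at least five of seven items must be at the top category, and only 19, 20 and 21 remain for moderate and all grades above it.

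**Step 3: the same cut-offs on a doubled score.** This is conditional, because the article does not state a doubling. A doubled score runs 0–42, and 2 × sum ≥ c is the same as sum ≥ c/2, rounded up.

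| Subscale | Raw sum needed if doubled | Share of 21 | Raw sums flagged only if doubled |
|---|---|---|---|
| Depression | 14/2 = 7 | 33% | 7–13 |
| Anxiety | 10/2 = 5 | 24% | 5–9 |
| Stress | 19/2 = 9.5, so 10 | 48% | 10–18 |

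Doubled sums are even, so a stress cut-off of 19 acts as 20. Everyone flagged on the raw sum is also flagged on the doubled sum. Omitting a required doubling can therefore only remove flags, on all three subscales.

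**Step 4: illustration of size, on assumptions that are not in the article.** The subscale sum is taken as beta-binomial on 0–21, with mean 3 to 9 and within-person correlation 0.1 to 0.3. Each cell shows the result for raw sums, then for doubled sums.

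| Subscale | Mean 5, correlation 0.2 | Expected flags among 12 | Range over the grid |
|---|---|---|---|
| Depression | 5% vs 32% | 0.6 vs 3.8 | 0–26% vs 12–72% |
| Anxiety | 17% vs 46% | 2.0 vs 5.5 | 3–45% vs 25–87% |
| Stress | 0.4% vs 17% | 0.1 vs 2.0 | 0–7% vs 3–45% |

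The width of the last column shows that the article does not determine the size.

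**The case against.** The strongest reply is that this is a condensed description of a standard instrument. The article names the Dutch version, cites sources for it, and never says that the cut-offs apply to unscaled sums. Unlike for the PSQI, it writes no denominator for the DASS-21. The team may follow the instrument's usual scoring, in which case nobody is misclassified. The primary outcome is feasibility, the post hoc sample size uses only the conditioned pain modulation and temporal summation data, and PSQI and HIT-6 are untouched. If the item responses are kept, a scoring slip can be corrected by recalculation.

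Most of this stands, and it limits the point. It does not remove it. The article does more than leave scoring to another document: it gives items, item range and thresholds as an apparently complete rule, and for stress that rule is implausible on its face.

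A reader might infer more: that only near-maximal scorers count on every subscale, that psychosocial deviation will be badly under-counted, or that people with severe symptoms will be missed. The document does not support these readings. Near-maximal is true of stress alone; 14/21 is two thirds and 10/21 just under half of the maximum. An under-count requires both that the cut-offs belong to a 0–42 scale and that the sums are not doubled in practice, and the article states neither. Severity bands above moderate do not appear in it, so nothing can be said about severe cases.

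**Conclusion.** The point holds as an unstated scoring scale with a visible mismatch, not as a demonstrated miscount. From the article alone, the described subscales reach at most 21, no rescaling is given, and the stress threshold at 19/21 fits a grade of moderate poorly. If the cut-offs are meant for doubled scores and raw sums are used, flags are lost on all three subscales and the profile proportions shift towards fewer deviating factors. That direction follows by arithmetic; the size depends on a score distribution that the article does not give. The effect is confined to the psychosocial profile and the secondary proportions built on it, which nevertheless feed the decision on expansion.

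**What to change.** Check in the instrument's manual which scale 14, 10 and 19 refer to, and state that scale in the same sentence as the cut-offs. If it is 0–42, say that each seven-item sum is multiplied by 2 before the cut-offs are applied, which is equivalent to raw sums of at least 7, 5 and 10. If it is not, correct the cut-offs or the scale description so that they agree. Build the confirmed rule into the scoring sheet before any participant is classified, and keep the item-level responses so that the flags can be recomputed. The cost is one sentence and one spreadsheet formula; no extra data are needed.

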#### Profiling-related outcome—pain profile

Participants will be categorised in four pain profiles based on responses to the TSP and CPM (figures 1–3):

P-P I: pronociceptive (increased TSP/impaired CPM).

P-P II: pronociceptive (normal TSP/impaired CPM).

P-P III: pronociceptive (increased TSP/normal CPM).

P-P IV: antinociceptive (normal TSP/normal CPM).

Each participant with CeH will be categorised into a pain profile per measurement location (TSP at the hand and face, CPM at the left and right suboccipital muscles).^49 50^ Additional presence of widespread pain will be evaluated (figure 4). The paragraphs below contain information on the definitions of increased/decreased TSP, impaired/normal CPM and presence of widespread hyperalgesia.

##### Pinprick stimulus: TSP

The pinprick evoked Wind-Up Ratio (WUR) (Pinprick stimulator, MRC Systems GmbH—Medizintechnische Systeme) is suggested to evaluate TSP. Participants will be positioned in sitting. The WUR will be assessed at the bilateral (ie, painful and pain-free sides) ophthalmic region (V1), and extrasegmentally on the thenar eminence of the dominant hand.^49 51–53^ WUR represents the quotient of pain intensity evoked by one single pinprick stimulus divided by the average pain evoked by 10 repetitive pinprick stimuli.^51–53^ We additionally propose to apply the SumSquare method as described by Allison *et al* to quantifying TSP.^54^ The WUR is reported to lack sensitivity to detect differences in the magnitude of sensitisation. Most studies report little variability (ratio 1.6–1.7) in WUR measurements both in normal and hyperalgesic states.^54^

For the measurements at the face and hand, constant pinpricks of 128 mN and 256mN, respectively will be used.^52^ First, a single pinprick stimulus will be applied, followed by a series of 10 pinprick stimuli with a frequency of 1 Hz within an area of 1 cm^2^.^50 52^ The interval between the single and repetitive stimuli will be 1 min, or until all aftersensations have resolved. Participants will be asked to rate the pain of a single pinprick stimulus, and the average pain at the end of the series of 10 pinpricks using the 0–10 Numeric Pain Rating Scale (0=no pain, 10=the worst pain imaginable). The test order will be standardised as: dominant hand—left side face—right side face. This procedure will be repeated three times at each site, and three measurements per site will be averaged (figure 2). We refer to the normative values provided by the German Research Network on Neuropathic Pain to determine normal or increased TSP at the face and hand.^51^ Test–retest reliability for pinprick induced TSP is moderate-to-good in healthy participants (ICC 0.51–0.61).^55^

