Dynamic protocols, to evoke inhibition or facilitation of pain, have been designed to evaluate endogenous pain modulation and to define a pronociceptive or antinociceptive central pain mechanism. Protocols to assess pain inhibition evaluate the conditioned pain modulation (CPM) paradigm, and pain facilitation assesses temporal summation of pain (TSP).^16^ The term CPM was created for psychophysical protocols that explore diffuse noxious inhibitory control in humans.^19^ The latter manifests as the inhibition of wide dynamic range neuronal activity by descending adrenergic pathways.^19^ CPM is measured by comparing pain induced by a test stimulus, with pain induced by the same test stimulus either during (parallel) or after (sequential) a conditioning stimulus. TSP is a nociceptive mediated process, which is considered to reflect advanced spinal synaptic facilitation in the dorsal horn (ie, behavioural correlate of wind-up).^20 21^ TSP is measured by comparing pain ratings between a single noxious stimulus and repeated equal-intensity noxious stimuli at a specific frequency. A third proxy to examine facilitated central pain mechanisms is widespread hyperalgesia.^22^

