### Limitations and suggestions

We acknowledge that assessing facilitated central pain mechanisms clinically is challenging for several reasons such as the absence of biomarkers to support its diagnosis. Although quantitative sensory testing is a promising surrogate measure to identify such facilitated mechanisms, it only evaluates evoked responses rather than spontaneous pain.^82^ Results should be interpreted within that context.

More research is needed into relevant modifiable psychosocial and lifestyle factors concerning sensitisation of pain in CeH.^86^ Sedentary time, anxiety, sleep quality, physical activity and stress were already reported to be associated with signs of central sensitisation in some people with CeH.^17^ Additionally, interindividual differences explain a large proportion of CPM variance.^87^ This finding forces researchers to look at the CeH population as more heterogeneous.^17 59^ We propose a feasibility study, which includes only 12 participants with CeH, which is the minimum recommended for pilot studies.^74^

Furthermore, WUR is reported to lack sensitivity to detect differences in the magnitude of sensitisation. Most studies report little variability (ratio 1.6–1.7) in WUR measures both in normal and hyperalgesic states. Therefore, we additionally propose to apply the SumSquare method as described by Allison *et al*.^54^ The potential future full-scale study should analyse endogenous pain modulation within a repeated-measures design to detect variance (ie, interindividual differences).^87^ Finally, using CPM, TSP and widespread hyperalgesia to compose the PMP can be time-consuming, expensive, and equipment is often not readily available in clinical practice. Therefore, the current protocol is an essential step towards further research (eg, assessing feasibility, validity, different populations), including development of easy-to-use alternative valid measurements to be widely implemented in clinical settings.

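### The wind-up ratio is defined upside down (single stimulus ÷ train), which contradicts the protocol's own 1.6–1.7 and, if applied literally, would misclassify temporal summation in the pain profile

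*Protocol article*

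**What the plan says.** The section 'Pinprick stimulus: TSP' gives the only formula for the index: "WUR represents the quotient of pain intensity evoked by one single pinprick stimulus divided by the average pain evoked by 10 repetitive pinprick stimuli". The ratings that enter it are described next: "Participants will be asked to rate the pain of a single pinprick stimulus, and the average pain at the end of the series of 10" (stimuli), each on a 0–10 scale.

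The same section reports the usual size of the ratio: "Most studies report little variability (ratio 1.6–1.7) in WUR measurements both in normal and hyperalgesic states". 'Limitations and suggestions' repeats the figure: "Most studies report little variability (ratio 1.6–1.7) in WUR measures both in normal and hyperalgesic states".

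The classification rule is external: "We refer to the normative values provided by the German Research Network on Neuropathic Pain to determine normal or increased TSP at the face and" (the second site is the hand). The article prints no numerical cut-off and does not say which side of the limit counts as increased.

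The direction of the construct is clear elsewhere. The Introduction pairs facilitation with this test ("pain facilitation assesses temporal summation of pain (TSP"), and the pain-profile section treats increased TSP as pronociceptive, for example "P-P III: pronociceptive (increased TSP/normal CPM". The Introduction's general description, "TSP is measured by comparing pain ratings between a single noxious stimulus and repeated equal-intensity noxious stimuli at a specific frequency", does not say which rating is divided by which.

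**The concern.** Temporal summation means that a series of equal stimuli hurts more than one of them. An index for which 'increased' means more facilitation must therefore rise as the train rating rises relative to the single rating. The written quotient does the opposite.

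This matters because TSP is one of the two axes that assign each participant, at each measurement location, to P-P I–IV. Under 'Statistics', the proportions in those profiles are the secondary analysis. Primary and secondary results together inform the decision to expand to a full-scale study, and TSP data are to feed the sample-size estimate for a larger trial. The formula is stated explicitly, so this is not a detail left to a fuller document. It conflicts with a figure in its own paragraph.

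**Working it through.** **Inputs**
- Written formula: WUR = S ÷ T, where S is the single-stimulus rating and T the average rating of the train of 10 ('Pinprick stimulus: TSP').
- Typical WUR: 1.6–1.7 (same section, and 'Limitations and suggestions').
- Increased TSP is pronociceptive ('Profiling-related outcome—pain profile').
- Example ratings (S, T) are illustrative and chosen for this check.

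**Step 1: can the written formula reproduce 1.6–1.7?** If S ÷ T = 1.6, then T = S ÷ 1.6 = 0.625 S. If S ÷ T = 1.7, then T = S ÷ 1.7 = 0.588 S. The train would hurt 37.5% to 41.2% less than one stimulus, which is the opposite of summation. With T ÷ S, the same values mean that the train hurts 60% to 70% more. Only T ÷ S fits the quoted figure as summation. Turned round, 1.6–1.7 would read 0.63–0.59 under the written formula.

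**Step 2: direction.**

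| S | T | Written, S ÷ T | T ÷ S |
|---|---|---|---|
| 2 | 3.3 | 0.61 | 1.65 |
| 2 | 4 | 0.50 | 2.0 |
| 2 | 6 | 0.33 | 3.0 |
| 4 | 2 | 2.0 | 0.50 |

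For non-zero ratings the two columns are reciprocals, so they rank participants in exactly opposite order (Spearman correlation −1.0).

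**Step 3: classification.** Let c be the upper normative limit on the T ÷ S scale, with c > 1 assumed. If pain rises over the train, T > S, so S ÷ T < 1 < c and the participant is called normal. Everyone with T ÷ S > c is in this group. Hence:
- true P-P I (increased TSP, impaired CPM) is recorded as P-P II;
- true P-P III (increased TSP, normal CPM) is recorded as P-P IV, the antinociceptive profile;
- the written formula flags only those with S ÷ T > c, whose pain falls over the train (for example 4 to 1.9, ratio 2.1).

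**Step 4: rough size, on assumed values.** T ÷ S was simulated as log-normal, centred at 1.65 with log-SD 0.2 to 0.5, against cut-offs from 2 to 4. T ÷ S flags 0% to 35% of participants as increased. The written formula flags 0% to 0.9%, and none of them are people flagged by T ÷ S. The centre, spread and cut-offs are assumptions; the absence of overlap follows from c > 1 alone.

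**The case against.** The best defence is that this is a slip of wording. The 1.6–1.7 in the same paragraph and the comparison with published norms show what is meant, and anyone who computed values near 0.6 would notice. That may be so. But no other passage gives the opposite formula or an inverted cut-off, so the written sentence remains the only operational definition for a team using or replicating the protocol.

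It can also be said that little is at stake. The primary outcome is feasibility, the profile proportions are descriptive in at least 12 participants, both ratings are recorded so the ratio can be recomputed without loss, and SumSquare gives a second TSP measure. All of this stands and limits the harm. SumSquare does not repair the profile, however, because nothing in the article ties it to the normal/increased decision.

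Some stronger readings are tempting but not supported:
- A reader might infer that the TSP categories are swapped one for one. Only the ranking is exactly reversed.
- A reader might infer that P-P I and P-P III would be empty. They could still hold participants whose pain falls over the train.
- A reader might infer that the larger trial's sample size will be wrong. 'Statistics' does not say whether WUR or SumSquare enters that calculation.
- A reader might also count as errors the lack of a rule for a single rating of 0, or of a statement whether ratings or ratios are averaged. An article may leave such details to the full protocol.

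**Conclusion.** The definition is wrong as written, and the article alone shows it: the formula is incompatible with the 1.6–1.7 it cites and with increased TSP being pronociceptive.

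The reversal of ranking needs no assumption beyond non-zero ratings. The effect on categories rests on two assumptions: that the sentence is applied literally, and that the normative limit, which the article does not print, is an upper one above 1. On those terms, no participant with rising pain can be classed as having increased TSP, and the secondary profile proportions would be wrong. The sample-size input would be wrong only if it uses WUR.

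The feasibility outcome, CPM, PPT and SumSquare are untouched, and an error found later could be undone from the raw ratings.

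**What to change.** In 'Pinprick stimulus: TSP', define WUR as the average pain of the 10-stimulus train divided by the pain of the single stimulus. Add that values above the normative upper limit mean increased TSP. Check that the analysis spreadsheet uses the same orientation before any profile is assigned.

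The cost is a sentence or two of text and one formula. No extra data, visits or tests are needed.
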